### 3 Version history

The first unblinded analysis of the TARGIT Trial took place in 2010 using a reference date of 02/05/2010, on the recommendation of the DMC. The emphasis was on efficacy and early safety. The results have been published (Lancet 2010; 376: 91-102).

The second unblinded analysis took place in 2012 using a reference date of 01/06/2012, on the recommendation of the DMC in 2010 (two years after the first analysis). The emphasis was on efficacy, and mortality. The results have been published (Lancet 2014; 383: 603–13).

This SAP is for a third unblinded analysis due to take place in 2019 using a reference date of 02/05/2018 on the recommendation of the TSC (completeness of follow-up at least 95% at 5 years and 90% at 10 years). The emphasis will be on all primary and secondary endpoints and subgroup analyses.

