### **7.2 Secondary Objectives**

To compare the treatment arms in each stratum with respect to:

- Overall survival (Breast Cancer and Non-Breast-Cancer Survival)
- Disease free survival
- Invasive-disease free survival
- Mastectomy and re-excision rate
- Treatment of local recurrence
- Site of relapse within the breast
- Local toxicity/morbidity

All outcomes in the following subgroups

- Effect of ER and PgR status on the outcomes
- Screen-detected vs symptomatic
- Effect of use of hormone therapy.
- Effect of Grade, node positivity, HER2 receptor status, etc.
- Effect of Centre and/ or Country on the outcomes
- Effect of all other predictive factors on the outcomes
- Re-do the relevant previously performed analyses with updated follow up information
- Outcomes as per treatment received along with subgroup analyses to refine understanding of what happens in the real world.

Additional analysis including Health economic analysis and cosmetic outcome, patient preference may also be undertaken.

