Analysis for all outcomes of the original (Lancet 2010) cohort of the first 2232 patients (mature cohort) as well as of the first 1222 patients (earliest cohort) who be expected to have completed a median follow up of 10 years. The following will be regarded as EXPLORATORY ANALYSES

**Regional recurrence:** Recurrence in the axilla or supraclavicular fossa

**Axillary recurrence with distant disease:** Recurrence in axilla concurrent with distant disease, or within 3 months of diagnosis of distant disease, or after diagnosis of distant disease.

To assess if there is adequate follow-up: The ratios of both  $N_f / (D_{all} - D_{cens}) > 95\%$  as well as  $N_f / D_{all} > 95\%$  will be used. If we find that this is impossible after adequate effort, we will have to reconsider the boundary with Trial Steering Committee.

Checks will be made for bias in follow-up by randomised treatment and/or by centre and statistical models will be used to assess the effect of such a bias. Additional analyses, tables and figures may be produced including analyses to assist in the determination of outliers, unusual data from specific centres or subgroups, skewness, kurtosis, etc. at the discretion of the Trial Statistician. Inclusion of such analyses, tables in the final report is optional. In addition, planned subgroup analyses will be performed for the main end points: local recurrence, local-recurrence-free survival, overall survival, breast cancer survival and non-breast-cancer survival for patients who are PgR positive vs. PgR negative and ER receptor positive vs. ER receptor negative, method of diagnosis (screening vs symptomatic), use of hormone therapy, and other predictive/prognostic factors.

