### 9.4 Statistical Analysis

The major endpoint is the incidence of local recurrence. This will be compared on the basis of 'intention to treat' (i.e. all randomised patients will be analysed) and the logrank test will be used. This will be performed once the baseline data have been compared to test the randomisation and to define whether any stratified analyses are required. In addition ratios of radiological lesion size to clinical and pathological size, and of specimen weight will be compared to ensure that the extent of the surgical procedure was similar in both groups. The baseline comparisons between the two groups will be done using chi-squared test for categorical variables and independent two sample t-test for all continuous variables. Statistical significance will be defined at the  $p < 0.05$  level. We will use Kaplan-Meier curves and proportional hazard regression models to account for time-to event and censoring of the data.

In addition, exploratory subgroup analyses will be performed on the main endpoint including variables such as tumour size, grade and axillary nodal involvement. These will be stipulated in the Statistical Analysis Plan agreed by the International Steering Committee before any analysis is undertaken.

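### The SAP calls its subgroup analyses planned and extends them to survival endpoints with an open factor list and no interaction test or multiplicity rule, whereas Protocol 9.4 makes them exploratory and fixed beforehand

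*Combined protocol and SAP*

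**What the plan says.** **Protocol 9.4** provides that "exploratory subgroup analyses will be performed on the main endpoint including variables such as tumour size, grade and axillary nodal involvement". These analyses are to be "stipulated in the Statistical Analysis Plan agreed by the International Steering Committee before any analysis is undertaken".

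**SAP section 3** gives the timing: "This SAP is for a third unblinded analysis due to take place in 2019", after unblinded analyses in 2010 and 2012. It lists subgroup analyses next to the primary and secondary endpoints as the emphasis of this round.

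**SAP section 10** says that "planned subgroup analyses will be performed for the main end points", which it lists as "local recurrence, local-recurrence-free survival, overall survival, breast cancer survival and non-breast-cancer survival". The factors are PgR status, ER status, "method of diagnosis (screening vs symptomatic), use of hormone therapy, and other predictive/prognostic factors".

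**SAP section 7.2** is wider still. It places subgroups among the secondary objectives under the line "All outcomes in the following subgroups", with a list that is also open-ended.

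**SAP section 6** has all results presented separately for the prepathology and postpathology strata. Neither SAP 8.2 nor section 10 specifies a treatment-by-factor interaction test, a significance level for subgroups or a multiplicity rule. The Cox model paragraph in section 10 says that significant factors will be reported.

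**The concern.** The two documents give the same analyses different standing. Under the protocol they are exploratory and listed in advance. Under the SAP they are *planned*, cover more endpoints, and include factors that are not named. An open class of factors is not a stipulated list, whichever date the protocol's timing condition refers to.

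This matters because the 2019 analysis reuses events already seen unblinded in 2010 and 2012. SAP 7.2 asks for earlier analyses to be redone with updated follow-up, and section 10 reanalyses the earlier cohorts. A subgroup that looked interesting in those rounds would be partly retested on the same events. If it appears under the word *planned*, with no interaction test and no count of how many contrasts were examined, a reader cannot tell a prespecified result from one that stood out by chance.

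**Working it through.** The plan states no error rate or power for subgroups, so there is no figure of its own to reproduce on this point. Its design calculation in Protocol 9.1 (1116 per arm) concerns the overall comparison only.

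**Step 1: compare the conditions.**

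| | Protocol 9.4 | SAP |
|---|---|---|
| Label | exploratory | planned (section 10); secondary objective (7.2) |
| Endpoints | main endpoint | five (section 10); all outcomes (7.2) |
| Factors | examples, to be listed in the SAP | four named, then open (section 10); open (7.2) |
| Timing | before any analysis | SAP for the third unblinded analysis |

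**Step 2: isolate the real extension.** Local recurrence is the protocol's main endpoint, and survival without local recurrence is the SAP's own primary endpoint (7.1, 8.2). The endpoints added are therefore overall, breast cancer and non-breast-cancer survival, which makes three.

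**Step 3: count the contrasts.** A subgroup effect is a difference in treatment effect between the levels of a factor, so each factor gives one contrast per endpoint and stratum:

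4 named factors x 3 survival endpoints x 2 strata = 24.

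**Step 4: false positives if no true interaction exists.** SAP 8.2 sets p < 0.025 for survival but does not tie it to subgroups. Applying it here is an assumption.

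- Expected number: 24 x 0.025 = 0.6. This does not depend on independence.
- Chance of at least one, all 24 independent: 1 - 0.975^24 = 0.46.
- Chance of at least one if the three endpoints behaved as one, leaving 4 x 2 = 8 independent contrasts: 1 - 0.975^8 = 0.18.

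The endpoints are correlated, since overall survival is made up of breast cancer and non-breast-cancer deaths. The truth should lie between 18% and 46% as far as endpoint correlation goes. Correlation between factors, such as ER with PgR, would lower it further. The unnamed factors and the repeats in earlier cohorts would raise it.

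**Step 5: sensitivity to correlation at the protocol's 0.05 level.** With four factors, all five endpoints and one stratum there are 20 contrasts. The chance of at least one false positive is 1 - 0.95^20 = 64% if they are independent. By simulation it is 55% at an endpoint correlation of 0.5 and 35% at 0.9. The same four factors on a single endpoint give 1 - 0.95^4 = 19%. Widening the endpoints raises the risk even under strong correlation.

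**The case against.** Several points on the other side are sound.

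- **A reader might infer that the SAP makes subgroup results confirmatory.** It does not. *Planned* means specified in advance. The SAP gives subgroups no alpha and no decision role, 8.2 makes the use of p values conditional, and it commits to displaying the results of all analyses.
- **A reader might infer that naming ER, PgR, method of diagnosis and hormone therapy breaches 9.4.** It does not. The protocol's variables are examples and the list is left to the SAP. Nor does 9.4 say that other endpoints are forbidden.
- **A reader might infer that these factors were picked after seeing the 2010 or 2012 results.** The documents cannot show this. SAP 8.1 refers to a SAP for the 2012-13 analysis whose subgroup list is not available here, and some factors may have been carried forward. The protocol's timing condition is itself open to reading, since Protocol 9.2 already reports an interim analysis reviewed in March 2010.
- **A reader might count each factor level separately.** That gives 48 comparisons, 48 x 0.025 = 1.2 expected false positives and 1 - 0.975^48 = 70%. That count is not apt: a within-level result is a false positive only if treatment has no effect in that level, and 48 such comparisons are far from independent.

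It can also be argued that the subgroups are already exploratory, because section 10 contains the line "The following will be regarded as EXPLORATORY ANALYSES". Regional and axillary recurrence follow that line directly. The follow-up adequacy criterion, the bias checks and a set of optional analyses come next, and only then the subgroup sentence, which introduces the subgroups as an addition and as *planned*. The heading does not clearly reach that far. At best the status is ambiguous.

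What remains after these points is the lost label, the added survival endpoints, the open list, and the absence of an interaction test or multiplicity rule.

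**Conclusion.** The discrepancy between Protocol 9.4 and the SAP is real and worth correcting. It concerns how subgroup findings may be read and leaves the primary conclusion untouched. The supportable claim is that a chance subgroup effect *could* be taken for a prespecified finding. The documents do not support saying that it would carry confirmatory weight, or that the factors were chosen after unblinding.

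For the named factors and the three added survival endpoints over two strata, 0.6 false positives are expected, with at most about a 46% chance of at least one. This assumes one contrast per factor, the 0.025 survival threshold applied to subgroups, and no true interaction. The 46% also assumes independence and falls with correlated endpoints.

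**What to change.** 1. In the subgroup sentence of SAP section 10, replace *planned* with *exploratory* for all subgroup analyses, except any documented in a cited SAP that predates the first unblinded analysis of 2010.
2. State that no significance claim will be drawn from the exploratory subgroups.
3. Report every subgroup examined as a treatment-by-factor interaction estimate with its confidence interval. Amend the Cox model paragraph in section 10, which now speaks only of reporting significant factors.
4. Apply the same exploratory label to the open-ended factors in SAP 7.2 and in the Cox model paragraph. Deleting a phrase in one place would not close the list, because the others stay open.
5. Keep all five endpoints. Confining subgroup reporting to local recurrence would drop the SAP's own primary endpoint, and 9.4 does not require it.

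The cost is a wording change. Subgroup results without an earlier documented plan lose their *planned* status. No data or analyses are given up.

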A cox- proportional hazard model will be used for analysis of any other predictive factors including variables such as age, tumour size, grade, HER2 status, axillary nodal involvement, vascular invasion, margin, whether screen detected or not. Influence of factors such as ASTRO and/or ESTRO criteria, timing of 1st surgery/biopsy in terms of menstrual cycle, time of the day of delivery of radiotherapy, height, weight, bra size, surgical technique and size of applicator used for TARGIT, dose prescription used for TARGIT, fractionation regime for EBRT, delay between initial surgery and delivery of TARGIT in the postpathology stratum, centre and country, use of systemic therapy, or other factors will also be explored provided sufficient data is available. Significant factors will be reported with absolute differences, and/or hazard ratios and 95%CI.

We shall also perform all the analysis for the first 1222 and 2322 patients recruited in the trial, referred to as the Earliest and Mature cohorts in the 2013/14 Lancet publication. We shall also perform these analyses for the first n number of patients in the pre-pathology stratum to enable a comparison with other trials of partial breast irradiation, where n matches the number of patients in those trials.

We shall describe completeness of follow-up, mastectomy rates, proportion of patients suspected and investigated to have local recurrence in each randomised arm, treatment of local recurrence, number of uncontrolled local recurrence at the time of death and use of EBRT in presence of high risk factors and the effect of radiation fractionation on toxicity. For completion, we shall analyse the cancer, toxicity, overall survival and non-breast-cancer survival outcomes as per treatment received (those that received only TARGIT, both TARGIT and EBRT and EBRT only), however, the results of these artificially created groups need to be interpreted with the consideration that TARGIT treatment is only recommended within a risk-adapted approach.

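### The SAP plans subgroup results and a Cox analysis of predictive factors but specifies no treatment-by-factor interaction, so prognostic factors could be reported as predictive

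*Combined protocol and SAP*

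**What the plan says.** SAP 7.2 lists the subgroup work under comparing the treatment arms within each stratum. The individual items, however, are worded as effects of factors on outcomes, for example "Effect of all other predictive factors on the outcomes".

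SAP Section 10 plans two kinds of analysis:

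- Subgroup analyses of five main endpoints: three on survival (overall, from breast cancer, and from other causes), local recurrence, and survival free of it. The receptor subgroups are given as "for patients who are PgR positive vs. PgR negative and ER receptor positive vs. ER receptor negative". Other splits are by how the cancer was detected and by "use of hormone therapy, and other predictive/prognostic factors".
- A regression analysis: "A cox- proportional hazard model will be used for analysis of any other predictive factors including variables such as age, tumour size, grade", with HER2, nodes, vascular invasion, margin and screen detection also named. A long further list is to be explored, including "size of applicator used for TARGIT, dose prescription used for TARGIT, fractionation regime for EBRT". The reporting rule is "Significant factors will be reported with absolute differences, and/or hazard ratios and 95%CI".

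Protocol 9.4 says that "exploratory subgroup analyses will be performed on the main endpoint including variables such as tumour size, grade and axillary nodal involvement" and adds: "These will be stipulated in the Statistical Analysis Plan agreed by the International Steering Committee before any analysis is undertaken". The SAP is therefore where the method belongs. Neither document, in the text available, mentions an interaction term, a test of heterogeneity, or a rule for separating predictive from prognostic factors.

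**The concern.** Whether a factor predicts benefit from IORT relative to EBRT is a question about the treatment difference: does it change across levels of the factor? A factor's own coefficient in a Cox model answers another question, namely whether the factor is associated with outcome across both arms together. Separate results per level do not answer the first question either, because a significant result in one level and a non-significant one in the other is not evidence that the two effects differ.

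This matters here because several listed factors are expected to be prognostic. Protocol 6.2.1.2 itself treats grade 3, lymphovascular invasion and node involvement as adverse. Such factors can reach significance when the treatment effect is identical in everyone. The trial compares a risk-adapted policy, and SAP 8.1 wants its results to help patients decide, so a prognostic factor labelled predictive could mislead about which patients do relatively better or worse with IORT.

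**Working it through.** **Plan's own figure.** The documents give no number for the factor or subgroup analyses. The only related design figure is the primary sample size in Protocol 9.1: (1.645 + 0.842)² × 2 × 0.06 × 0.94 / 0.025² ≈ 1116 per arm, which reproduces. This point does not depend on it.

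**Inputs.** SAP Section 6 requires results by stratum. The documents give 3,451 patients in total but no stratum sizes, so 2,300 is an assumption. Also assumed are an overall event rate of 1.5% or 3%, factor prevalence of 20% or 30%, and a prognostic ratio of 2 or 3. SAP 8.2 sets p<0.001 for local recurrence and p<0.025 for survival without saying whether these govern the factor tests, so both 0.05 and 0.001 are shown.

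**Method.** Events in the four arm-by-factor cells are treated as Poisson, with Wald tests on log rates and 40,000 simulated trials per scenario.

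**Step 1: factor term, no treatment effect and no effect modification.** With E events and prevalence p, the share of events in the factor-positive level is p·r / (p·r + 1 − p). The test statistic is centred at ln(r) / √(1/e₁ + 1/e₀).

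- Lowest case: E = 2,300 × 0.015 = 34.5, p = 0.2, r = 2. The share is 0.4/1.2, so e₁ = 11.5 and e₀ = 23. The SE is √(1/11.5 + 1/23) = 0.361 and z = 0.693/0.361 = 1.92. Power at 0.05 is Φ(1.92 − 1.96) = 0.48 (simulated 0.48). At 0.001 it is Φ(1.92 − 3.29) = 0.09 (simulated 0.10).
- Highest case: E = 69, p = 0.3, r = 3. The share is 0.9/1.6, so e₁ = 38.8 and e₀ = 30.2. The SE is 0.243 and z = 1.099/0.243 = 4.53. Power is above 0.99 at 0.05 and 0.89 at 0.001 (simulated 0.99 and 0.89).

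**Step 2: interaction.** With no effect modification the log ratio of rate ratios is centred at zero, with variance equal to the sum of 1/events over the four cells. The test therefore rejects at about its nominal level.

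**Step 3: separate subgroup tests when IORT doubles recurrence equally in both levels.** P(disagree) = q₁(1 − q₂) + q₂(1 − q₁), where q is the power in each level. Example: EBRT rate 3%, p = 0.2, r = 2. EBRT events are 11.5 and 23, and IORT events are 23 and 46. The SEs are 0.361 and 0.255, so at 0.05 q₁ = 0.48 and q₂ = 0.78. P(disagree) = 0.48 × 0.22 + 0.78 × 0.52 ≈ 0.51 (simulated 0.51).

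| 2,300 patients (simulated) | 1.5% rate | 3% rate |
|---|---|---|
| Factor term significant, p<0.05 | 48–89% | 74–99% |
| Factor term significant, p<0.001 | 10–46% | 30–89% |
| Interaction rejects, p<0.05 | 4–5% | 5% |
| Subgroups disagree (IORT doubles), p<0.05 | 47–49% | 45–51% |
| Subgroups disagree (IORT doubles), p<0.001 | 2–4% | 24–28% |

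In the last two rows the rate is that of the EBRT arm. With all 3,451 patients pooled, the factor term is significant in about 63–97% of trials (1.5%) and 89% to over 99% (3%) at p<0.05.

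**Step 4: cost in power.** For a true ratio of hazard ratios of 2, with a share f of the events in one level, SE = √(4/(E·f) + 4/(E(1 − f))). At E = 60 and f = 0.5 this is √(4/30 + 4/30) = 0.516, so power is Φ(0.693/0.516 − 1.96) = 0.27. Over f = 0.2–0.5, power is 0.19–0.27 at 60 events and 0.50–0.69 at 200.

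**The case against.** The strongest reply is that this is a gap, not a stated wrong method. The SAP lists no Cox terms, so an interaction is unspecified rather than ruled out, and no null hypothesis is written for these factors. The word predictive is used loosely, since the subgroup paragraph runs predictive and prognostic together. If the aim is simply to describe how factors relate to outcome, a factor-only model fits and only the label is at fault. Protocol 9.4 calls the subgroup analyses exploratory. SAP 8.1 and 8.2 favour absolute numbers by arm, make p values optional and promise to show all results. At the SAP's p<0.001, a factor with ratio 2 at a 1.5% event rate is significant in only about 10% of simulated trials.

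Most of this stands as a limit on the claim. A reader might infer that the SAP commits to testing main effects, that prognostic factors will inevitably be reported as predictive, or that they will be used to select patients for IORT. The documents say none of these things. It also stands that an arm interaction cannot be estimated for factors that exist in one arm only.

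It does not remove the gap. The lead-in to SAP 7.2 is a comparison of arms. SAP Section 10 calls the subgroup analyses planned and selects factors for report by significance. Exploratory status does not make a main effect, or a pair of subgroup p values, answer a question about heterogeneity. If predictive is only loose wording, the ER, PgR, grade and node comparisons still lack a test of whether the treatment effect differs. The promise to display everything sits uneasily with a rule that reports significant factors.

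**Conclusion.** The point holds as an omission with a real risk of misreporting. The SAP sets out to compare arms across factor levels but specifies no analysis of whether the treatment effect differs between them. Following its reporting rule could present prognostic factors as predictive and apparent subgroup differences as real.

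The size depends on assumed event counts, prevalence, prognostic strength and stratum size, and on which p threshold applies. At p<0.001 and low event rates the risk is modest. The direction does not depend on these inputs: without effect modification, only the interaction test keeps its error rate near or below nominal. These are secondary analyses, so the primary comparison is unaffected, but the SAP should be changed.

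**What to change.** In SAP Section 10:

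- For each factor defined in both arms and fixed before or at surgery, fit within each stratum a Cox model with randomised arm, factor and their product. Report the ratio of hazard ratios with 95% CI and p value, beside the 5-year absolute risk by arm in each level.
- Do this for every listed factor, not only significant ones. Call a factor predictive only on the interaction, label main effects prognostic, and label the whole set exploratory.
- Report applicator size, TARGIT dose prescription, delay to TARGIT and EBRT fractionation as within-arm associations.
- Keep the hormone and systemic therapy subgroups, flagged as post-randomisation and descriptive.
- Note that surgical pathology in the prepathology stratum is measured after randomisation. Protocol 3.1 accepts that knowledge of the allocation may influence the excision, which bears on margin status in particular.

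The cost is SAP wording and one model term per factor, with no new data. The drawback is low power: most factors will show no clear evidence of a different effect, and this should be worded as absence of evidence, with the interval shown.
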